### Participants

Inclusion criteria for schools are: 1) no previous RUBIES or HELM exposure; 2) identification of at least two autistic children with co-occurring externalizing behavior prior to study enrollment, 3) principal/administrator agreement to randomization, and 4) principal/administrator agreement to participate in HELM, if assigned to that condition.

### Leaders and educators

An anticipated total of 373 participants from 42 public elementary schools in the USA will be enrolled in the proposed study. This includes 126 educators who will receive either RUBIES or educator psychoeducation and 126 autistic children yoked to those educators. It also includes 28 first-level leaders, 9 district administrators, and 84 additional educators (3 per school) who will complete 360° assessments of school leadership and climate in the HELM and RUBIES only conditions over the course of the study. Participants will remain in the study for two years, unless they are randomized to psychoeducation (enrollment concludes at the end of Year 1) or withdraw or change jobs.

Educators are eligible for inclusion if they are special or general education teachers, paraeducators, or other staff (e.g., speech therapist, school psychologist) at a public elementary school who provide direct instruction and/or behavioral support to autistic children during the school day. For the 28 schools randomized to RUBIES + HELM or RUBIES only, approximately three additional educators (e.g., teachers, paraeducators, specialists, counselors) involved with autistic students will be recruited per school to complete the 360° assessments of implementation leadership and climate at each time point (*n* = 84 additional educators), one to two principals or school administrators will be recruited per school, and one to two district administrators will be recruited per district. District leaders will be requested not to use HELM strategies with participating schools randomized to other conditions. No participants will be excluded based on sex, age, or racial/ethnic background.

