### Hypothesis 3b

Increases in principal implementation leadership and school implementation climate will mediate HELM’s effect on educator sustainment relative to RUBIES coaching alone (arm 1 vs. arm 2).

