## Method

### Study design

This study will use a hybrid type 2 effectiveness-implementation trial with HELM, RUBIES, and a psychoeducation only control condition to provide a rigorous test of the effects of RUBIES and HELM across 126 educators paired with 126 autistic children in 42 elementary schools. The full sample of 42 elementary schools will be enrolled in three cohorts of approximately 14 schools each nationwide. Each cohort will participate for two years. Depending on arm, educators will complete study instruments up to six times: 1) Spring semester prior to the year of school and student enrollment (implementation baseline; arms 1–2); 2) Fall semester Year 1 (clinical baseline; arms 1–3); 3) 16 weeks (arms 1–3); 4) 24 weeks (arms 1–3); 5) 52 weeks (arms 1–2); and 6) 76 weeks (arms 1–2). Leaders and educators will be compensated $40 at implementation and clinical baseline, $50 at Week 16, $60 at Week 24, $70 at Week 52, and $80 at Week 76 for the completion of study instruments at each timepoint. See Fig. 3 for study design.

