### Randomization

The biostatistician (WS) will generate the random allocation sequence; all other research team members will not have access to the randomization sequence. Schools in each cohort will be randomized (1:1:1) to one of three parallel arms (*n* = 14 schools per arm): 1) RUBIES + HELM; 2) RUBIES only; 3) or educator psychoeducation. Randomization will be stratified based on median split for: 1) size of school at the time of enrollment; and 2) number of possible dyads (identified at screening for each enrollment cohort). Study enrollment, randomization, and engagement for all schools begins in the Spring prior to Year 1. Schools randomized to psychoeducation will be enrolled in the trial for one year; schools randomized to either RUBIES + HELM or RUBIES only will be enrolled in the trial for two years; children will be enrolled for one year.

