### Implementation strategies

#### HELM

Members of the research team will work with school principals and district-level leaders who participate in HELM over the course of 9 months [33]. HELM includes eight components: 1) Assessment and Feedback. Principals, assistant principals, and educators familiar with RUBIES will complete an initial 360º survey on RUBIES implementation leadership and climate in the spring semester prior to the year of enrollment (HELM baseline, Year 0), Weeks 16, 24, 52, and 76. A detailed feedback report will be shared with the leader, to create a personal leadership development plan to support implementation and sustainment; 2) Initial Training. Principals, assistant principals, and district leaders will participate in didactic and interactive trainings on developing strategic implementation leadership behavior and an EBP implementation climate in their schools in the summer prior to Year 01 of study enrollment; 3) Leadership Development Plan. Principals will work with their coach to review their 360º assessment data and develop goals for improving implementation leadership and climate during the initial training and during coaching; 4) Individual Coaching. A former principal will provide monthly 1-h one-on-one coaching sessions via Zoom with the principals and assistant principals to review progress and update the leadership development plan. 5) Group Coaching. A former principal will offer optional monthly 1-h group coaching calls with HELM principals to review progress and share strategies across schools; 6) Organizational Strategy Meeting. Two, 1-h meetings with principals and district-level leaders will be held in each semester of Year 01, to develop and update an organizational implementation strategy plan. This meeting will provide a structured discussion of alignment between school- and district-level efforts to support RUBIES implementation and sustainment; 7) Professional Learning Collaboratives. Two professional learning collaboratives will be held with principals in Year 01 to review content (align HELM strategies with principles from the National Educational Leadership Standards, and EBP sustainment) and share strategies; and 8) Graduation. Principals’ final feedback will be reviewed, progress for the past year will be celebrated, and sustainment plans will be reviewed.

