#### HELM mediators

Educators will complete the School Implementation Leadership Scale (S-ILS) [55], a 21-item measure that assesses seven subscales of implementation leadership: knowledgeable (understanding of RUBIES and implementation issues), supportive (support for RUBIES use), proactive (anticipating and addressing challenges), perseverant (consistent and responsive to challenges), communicative (shares implementation related information with staff), has a vision/mission (oriented towards using RUBIES), and available in implementing RUBIES [5, 37]. The S-ILS is a psychometrically validated and reliable instrument (α = 0.95–0.98). Implementation leadership scores are generated for a school at each timepoint (implementation baseline, Weeks 16, 24, 52, and 76) by aggregating individual educator ratings to the school level.

Educators also will complete the School Implementation Climate Scale (S-ICS) [56], a 21-item measure that assesses seven subscales of implementation climate: focus, educational support, recognition, rewards, use of data, existing supports, and RUBIES integration [37, 56]. The S-ICS is a psychometrically validated and reliable instrument (α = 0.81–0.91; 39, 79). Implementation climate is scored by aggregating individual educator ratings to the school level.

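### The leadership and climate raters, and their baseline, come after assignment to arm 1 or 2, and only HELM schools are described as feeding results to the rated leader, so the Aim 3 test of HELM on its mediators is open to rater-selection and reporting bias

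*Protocol article*

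**What the plan says.** All places are in the protocol article.

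- **Raters.** Leaders and educators plans for "84 additional educators (3 per school) who will complete 360° assessments of school leadership and climate in the HELM and RUBIES only conditions" and describes their recruitment as "For the 28 schools randomized to RUBIES + HELM or RUBIES only, approximately three additional educators". The psychoeducation arm has no such raters.
- **Assignment.** Randomization describes one step: "Schools in each cohort will be randomized (1:1:1) to one of three parallel arms". On timing it says "Study enrollment, randomization, and engagement for all schools begins in the Spring prior to Year 1".
- **Baseline.** Study design lists the first data collection as "Spring semester prior to the year of school and student enrollment (implementation baseline; arms 1–2". The footnote to Table 1 likewise limits the leadership and climate scales to the two RUBIES arms.
- **Feedback.** The 360° survey is the first of the eight HELM components, repeated at Weeks 16, 24, 52 and 76. Of its results, the HELM section says: "A detailed feedback report will be shared with the leader, to create a personal leadership development plan to support implementation and sustainment". No such report is described for RUBIES-only schools.
- **Use as mediator.** Under HELM mediators, "Implementation leadership scores are generated for a school at each timepoint (implementation baseline, Weeks 16, 24, 52, and 76) by aggregating individual educator ratings". Climate is scored the same way. Hypothesis 3b states: "Increases in principal implementation leadership and school implementation climate will mediate" the HELM effect on sustainment, arm 1 against arm 2.
- **Status of the test.** The Aim 3 analysis text makes the effect of HELM on these mediators part of its primary focus and calls the rest of the mediation chain exploratory.
- **Masking.** A masked independent evaluator is named for the BSPI, CGI-I and CGI-SM. None is named for the educator ratings.

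**The concern.** One survey has two jobs. In arm 1 it is part of the intervention, and its results go to the leader being rated and into that leader's coaching. In both arms it is the measurement on which HELM's mechanism is judged. Staff in the two arms therefore fill in the same form under different described conditions, across exactly the contrast being tested.

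Two biases could follow. First, whoever picks or agrees to be a rater may do so differently once the school is known to be a HELM school. Second, staff may answer more leniently when the rated leader will see the results. Either would look like better leadership or climate.

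The Spring score is not a clean starting point either, because it too follows assignment. An inflated arm 1 baseline could equally hide a real HELM effect on change. The mechanism evaluation is a stated purpose of the trial, so the quality of this comparison matters.

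**Working it through.** **Counts.** 28 schools × 3 = 84 raters, and 126 + 126 + 28 + 9 + 84 = 373 participants. Both match Leaders and educators. No sample size or power figure is in dispute; the Aim 3 power calculation covers only the RUBIES mediator.

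**Order of events.** Arm 3 has neither the extra raters nor the implementation baseline, so at least the split between RUBIES and psychoeducation must be known before either step. Randomization describes a single three-way allocation with no staged release, so the HELM assignment exists at the same moment. Whether it is also known to schools and raters at that moment is an inference; the article does not say. HELM training starts in the summer, after the Spring baseline, so that baseline can reflect knowledge of the arm but not the training.

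**Size of a possible bias.** The documents give 14 schools per arm. The reporting shift *s* (in SDs of the school mean score) and the correlation ρ between baseline and follow-up school scores are assumptions, because the documents give neither. The true HELM effect is set to zero, and tests are two-sided at 5%.

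1. *Follow-up scores only, no baseline.* t test, 26 df, noncentrality = s / √(2/14).
   - s = 0.3: 0.3 / 0.378 = 0.79, false positives 11.9%.
   - s = 0.5: 0.5 / 0.378 = 1.32, false positives 24.7%.
2. *Shift present at baseline and follow-up, baseline as covariate.* The remaining shift is s(1 − ρ) against a residual SD of √(1 − ρ²). For s = 0.3 and ρ = 0.3 that is 0.21 against 0.954; for ρ = 0.7 it is 0.09 against 0.714.
3. *Shift at follow-up only, baseline as covariate.* The whole shift s stands against the smaller residual SD √(1 − ρ²).

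Simulated false-positive rates for cases 2 and 3 (14 against 14 schools, covariance analysis with 25 df, 200,000 trials per cell; the rate with no shift was 5.0%):

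| s | ρ | Shift at both times | Shift at follow-up only |
|---|---|---|---|
| 0.3 | 0.3 | 8.5% | 12.4% |
| 0.3 | 0.5 | 7.1% | 13.9% |
| 0.3 | 0.7 | 6.1% | 18.2% |
| 0.5 | 0.3 | 14.4% | 25.8% |
| 0.5 | 0.5 | 10.9% | 30.3% |
| 0.5 | 0.7 | 8.0% | 41.5% |

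The noncentral t approximation for the same cells runs slightly higher (for example 8.7% for the first cell) because it ignores the precision lost to baseline imbalance.

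**Scale.** With 3 raters and an assumed within-school correlation of 0.1 to 0.3, the SD of a school mean is √(0.1 + 0.9/3) = 0.63 to √(0.3 + 0.7/3) = 0.73 rater SDs. A shift of 0.3 school-level SD is then about 0.19–0.22 rater SD, and 0.5 is about 0.32–0.37.

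**The case against.** The strongest reply has five parts.

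- **The baseline absorbs much of it.** Selection of supportive raters, or leniency already present in Spring, affects the first survey too. A constant shift cancels in a change score and shrinks under baseline adjustment. This stands. A reader might take 12% and 25% as the general size of the problem, but those figures belong to an analysis that ignores the baseline.
- **The order is inferred.** HELM status could be withheld from schools until after the Spring survey, and the full protocol may say so. This stands as a limit on certainty. It does not remove the point, because the article describes one three-way allocation and recruits raters by its result.
- **Both compared arms recruit under one rule.** True, so selection bias needs choices that differ by HELM status, and the article does not say who chooses. The feedback report, however, is described for one arm only, whatever the recruitment rule.
- **The reach is limited.** A reader might infer that the sustainment result, or a finding of mediation, could be produced by reporting alone. The documents do not support that. The BSPI is rated by a masked evaluator, and a uniform shift in ratings cannot create a link between mediator and BSPI. If that link exists for its own reasons, an inflated first path would carry into the product of coefficients, but the plan labels that step exploratory.
- **Feedback defines HELM, and climate is by definition shared perception.** Fair. Some change in ratings is the construct itself, so the point is stronger for leadership than for climate. Nor does the article say that leaders see individual ratings; the report may already be pooled.

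**Conclusion.** The point holds as a risk to one analysis: the primary Aim 3 comparison of leadership and climate between HELM and RUBIES-only schools. Raters not described as masked are recruited, and their baseline is taken, after schools are assigned, and only one arm is described as returning results to the rated leader.

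The documents do not show that bias will occur, and they give no figure for it. Under assumed shifts and a baseline–follow-up correlation of 0.3 to 0.7, a nominal 5% test would give about 6–9% false positives for a 0.3 SD shift present at baseline and adjusted for, and about 12–18% if the shift arises only at follow-up. For 0.5 SD the ranges are about 8–14% and 26–42%.

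The primary clinical outcome, the masked BSPI outcome and the mediator-to-BSPI path are not affected. The change is worth making but is not critical to the trial's main conclusions.

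**What to change.** 1. Ask each school for a staff list before the HELM versus RUBIES-only assignment is released, and have the research team settle the raters from it, preferably at random.
2. Release assignment in two steps: RUBIES versus psychoeducation first, then HELM versus RUBIES only once the Spring S-ILS and S-ICS baseline is complete.
3. Give raters in both arms the same confidentiality notice, and report only school-level aggregates to leaders.
4. State as a limitation that leniency arising after baseline from the HELM feedback loop remains, so the mediator effect may partly reflect reporting.

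Steps 1 and 2 remove arm-dependent choice of raters and give a true pre-assignment baseline. They do not cure leniency. A lenient shift that would otherwise sit in both scores would then appear only at follow-up, which is the less favourable column of the table. Steps 3 and 4 are therefore needed alongside them.

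The cost is a staff list, a disclosure sequence and one notice, with no added visits, raters or measures. The downside is slightly later HELM scheduling in the Spring. Training starts only in the summer, and the Discussion reports no enrolment as of February 2026, so the change still fits the calendar.

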### Autistic children

Enrolled educators will identify one autistic child with whom they currently work for potential enrollment in the trial. Educators will share information about the study with the child’s caregiver/legal guardian and ask to share the caregiver’s contact information with the research team to complete informed consent. Consenting caregivers will be contacted by the research team. All study activities will be described verbally and in writing during the caregiver informed consent process. The research staff will describe the study and expected roles and responsibilities, risks and benefits, and confidentiality procedures and will obtain electronic parent/guardian consent. Autistic children enrolled in the trial will be paired with one educator (1:1 dyad). We anticipate recruiting at least two autistic children per school (range 2–5 children per school). Inclusion criteria for children are: 1) a documented autism diagnosis via school records (i.e., Individualized Education Program; IEP); 2) enrolled with a participating educator; 3) in grades K-5; ages 5–12; and 4) a Sutter Eyberg Student Behavior Inventory-Revised (SESBI-R) [43] total score ≥ 101 and/or an Emotion Dysregulation Inventory [44] sum score of ≥ 8 at baseline as rated by the educator after the dyad consents. Educators will be excluded if their principal/administrator declines participation. If an educator serves no autistic children who meet eligibility criteria, the educator will be excluded.

### Procedures

#### Recruitment

Recruitment of public elementary schools will occur in multiple stages – the research team will: (1) meet with school district officials to obtain a list of elementary schools that serve autistic children in Kindergarten through fifth grade; (2) contact the principal at each prospective school to share information about the study and set up an initial meeting; and (3) work with school district officials and principals to set convenient times to deliver RUBIES and HELM, if randomized to those conditions. All participants will provide electronic informed consent. Schools will be compensated $400 to support enrollment and allow educators time to complete study activities.

## Clinical interventions

### Rubies

RUBIES is a manualized, 9-session educator-delivered intervention that addresses externalizing behaviors in autistic children [45, 46]. Although RUBIES follows a standardized manual, behavioral strategies are tailored to the autistic student, informed by target behaviors and their hypothesized function, as well as child- and educator-specific classroom needs. One goal of RUBIES is for educators to build mastery over a set of behavioral skills that are used to support the student currently under their care with potential to generalize to other autistic students in their classrooms. RUBIES also focuses on engaging the student’s broader educational team through an initial collaborative planning session as well as targeted goals in every session focused on activating a weekly team communication and generalization plan. Sixteen weeks will be allotted to complete the 9 modules, to account for cancellations, scheduling conflicts, holidays, etc. Educators will receive a RUBIES workbook, access to an online platform that houses resources (e.g., extra copies of activity sheets, video models of an educator implementing RUBIES strategies), and a toolkit with recommended sensory tools and premade visual supports to accompany RUBIES use. Educators will engage in RUBIES sessions with a coach who has a master’s degree or higher and completed training to fidelity in RUBIES (i.e., manual review, viewing of RUBIES sessions, co-leading sessions with a certified RUBIES-trainer). The coach will facilitate weekly hour-long RUBIES sessions with educators via Zoom at a convenient time. Coaching sessions will include a practice plan review, didactic instruction on behavioral strategies, and coaching and consultation to tailor newly learned strategies. Educators will be offered a Booster session at three time points during Year 02. Booster sessions will involve reviewing three main components of RUBIES: conducting a functional assessment, prevention strategies, and how to implement more effective responses to challenging behaviors.

### Educator psychoeducation

Autistic children in schools assigned to the educator psychoeducation condition will receive standard of care school-based interventions (no research intervention). Participating educators in schools randomized to this condition will receive an online, self-paced webinar program via a web-based learning portal. The program includes 8-modules on supporting autistic children in schools, without discussion of behavioral management strategies: 1) Introduction to Autism, 2) Autism in Schools, 3) Interventions for Supporting Communication, 4) Executive Functioning, 5) Inclusion in Schools, 6) Autism EBPs, 7) Social Functioning in Autism, and 8) Recess Engagement Strategies. Each module is 20–35-min long.

### Implementation strategies

#### HELM

Members of the research team will work with school principals and district-level leaders who participate in HELM over the course of 9 months [33]. HELM includes eight components: 1) Assessment and Feedback. Principals, assistant principals, and educators familiar with RUBIES will complete an initial 360º survey on RUBIES implementation leadership and climate in the spring semester prior to the year of enrollment (HELM baseline, Year 0), Weeks 16, 24, 52, and 76. A detailed feedback report will be shared with the leader, to create a personal leadership development plan to support implementation and sustainment; 2) Initial Training. Principals, assistant principals, and district leaders will participate in didactic and interactive trainings on developing strategic implementation leadership behavior and an EBP implementation climate in their schools in the summer prior to Year 01 of study enrollment; 3) Leadership Development Plan. Principals will work with their coach to review their 360º assessment data and develop goals for improving implementation leadership and climate during the initial training and during coaching; 4) Individual Coaching. A former principal will provide monthly 1-h one-on-one coaching sessions via Zoom with the principals and assistant principals to review progress and update the leadership development plan. 5) Group Coaching. A former principal will offer optional monthly 1-h group coaching calls with HELM principals to review progress and share strategies across schools; 6) Organizational Strategy Meeting. Two, 1-h meetings with principals and district-level leaders will be held in each semester of Year 01, to develop and update an organizational implementation strategy plan. This meeting will provide a structured discussion of alignment between school- and district-level efforts to support RUBIES implementation and sustainment; 7) Professional Learning Collaboratives. Two professional learning collaboratives will be held with principals in Year 01 to review content (align HELM strategies with principles from the National Educational Leadership Standards, and EBP sustainment) and share strategies; and 8) Graduation. Principals’ final feedback will be reviewed, progress for the past year will be celebrated, and sustainment plans will be reviewed.

